### Outcome measures

The following primary and secondary self-report outcome measures will be provided by blinded research assistants at baseline and 3, 6, 9 and 12 months in the form of printed questionnaires sent by postal mail and/or electronic versions of the questionnaires emailed to participants.

#### Primary outcome measures: pain intensity

Our primary outcome measure will be pain intensity measured at 12 months using the Low Back Pain Rating Scale and a 100-mm visual analogue scale. The Low Back Pain Rating Scale is a valid measure of pain [14]. It consists of three 11-point box scales measuring current pain, the worst pain within the last 2 weeks and average pain within the last 2 weeks. These three scores are measured and averaged. The Low Back Pain Rating Scale was used in the previous trial by Albert et al. [6], enabling calculation of study sample size and comparison of results.

#### Secondary outcome measures: disability, work absenteeism and hindrance in work performance

Disability will be assessed using the Roland Morris Disability Questionnaire, which is a validated instrument designed to assess self-rated disability caused by low back pain [15]. We will examine absenteeism and hindrance in the performance of paid and unpaid work using The Short form Health and Labour questionnaire. This is a validated questionnaire used to collect data on productivity losses due to injury or sickness in individuals involved in paid or unpaid work [16].

##### Global improvement

A 6-point scale, ranging from ‘much worse’ to ‘completely recovered’ will be used to assess global improvement [17].

##### General health status

General health status will be measured using the EuroQol Instrument (EQ-5D-5L) [18].

##### Depression

Severity of mood symptoms will be assessed using the Beck Depression Inventory [19].

##### Fear of movement/(re)injury

Fear of movement/(re)injury will be examined using the 17-item Tampa scale [20].

### Potential explanatory factors

#### Anthropometry

Height (stadiometer), weight (electric scales) and body mass index (height/ weight^2^) will be measured at baseline.

#### Physical activity

The International Physical Activity Questionnaire short version [21] will be used to assess physical activity.

#### Concomitant medication use

The use of non-opioid analgesics and non-steroidal anti-inflammatory drugs will be allowed during the trial. The randomisation process is the most effective method for ensuring 2 groups are as similar as possible with respect to known confounders and unknown potential confounders including treatments. We will also collect data on the medication used and adjust for this in the analyses.

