### Sample size calculation

#### Primary outcome: reduction in pain intensity

With 85 patients in each arm of the trial, there will be 90% power to detect a difference of 0.50 standard deviations in our primary outcome measure of pain. For the Low Back Pain rating scale, and assuming a between-person *SD* of 3.0 [6], a difference of 1.5 units can be detected with 90% power. A clinically significant difference in pain intensity is regarded as being at least 2 units [23].

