#### Presence of Modic changes

For the secondary aim of assessing whether the effect of antibiotics compared to placebo is dependent on the presence of Modic changes, the relevant power calculation is that for detecting an interaction between antibiotic intervention and Modic status. We anticipate half the patients will demonstrate Modic changes at baseline, and assuming a between-person SD of 3.0 in LBP rating scale [6], 85 patients per randomised arm will have 80% power to detect an interaction effect of size 2.6, meaning that the effect of antibiotics in patients with Modic changes is 2.6 units higher than in patients without Modic changes. The value of 2.6 was observed in Albert et al. [6], and therefore, there is sufficient power to detect a large antibiotic effect in the Modic changes subgroup compared with little effect, if any, in other patients. If there is a significant interaction effect between antibiotic effect and Modic changes, this will provide evidence to support the hypothesis that infection is important in the underlying pathogenesis in this subgroup of patients with chronic low back pain and disc herniation. All analyses will adjust for the baseline value of the relevant outcome variable, and this will further increase the power by an amount depending on the size of the baseline to follow-up correlation in the outcome.

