### Statistical analysis

Summary statistics comparing randomised arms at baseline will be tabulated. Intention-to-treat analyses of primary and secondary continuous outcomes will be performed by linear regression adjusting for the baseline of the outcome variable. Logistic regression will be performed for binary outcomes. Adjustment for imbalanced baseline factors, including the presence of symptoms other than low back pain, will be performed as supplementary analyses. We will perform a per-protocol analysis as a secondary analysis, defining compliance to the protocol as taking ≥ 80% of the planned number of pills, which is consistent with methodology from a previous trial [7]. Analysis of the moderating effect of Modic change status will use regression models with an interaction term between intervention arm and Modic change status, and adjusting for baseline values of the outcome variables. Missing outcome data for all analyses will be imputed via multiple imputation methods using relevant baseline and post-baseline measurements.

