There has been variation between the clinical trials in the additional care participants are allowed to access. While participants in the Albert et al. trial were not allowed to seek other treatments during the 1-year trial period [6], those in the Bråten et al. trial were permitted to continue ongoing treatment, but recommended not to start additional treatments or use non-steroidal anti-inflammatory drugs [7]. We have chosen to allow participants in both groups to seek usual care, including the use of analgesia and non-steroid anti-inflammatory medication. We do not expect usual care to affect the proposed mechanism of the antibiotic therapy that is being tested in this trial and usual care to be balanced across the treatment groups due to randomisation. All care provided to each individual patient in both groups will be documented.

The previous clinical trials of antibiotics both targeted patient subgroups with disc herniation and Modic changes, but with Albert et al. recruiting patients with type 1 Modic changes only [6] and Bråten et al. including those with type 1 or 2 Modic changes [7]. It is hypothesised that Modic changes result from a bacterial infection in the disc with cytokine and propionic acid production causing inflammation in the adjacent bone. While a biopsy study by Albert et al. has shown that 80% of individuals with infected disc material developed new Modic changes [24], it is unclear whether Modic changes are important in patient selection. In the biopsy study, low virulent bacteria were also identified in participants who did not develop new Modic changes, and conversely, those that had no bacteria present also developed Modic changes [24]. Moreover, our systematic review found that disc herniation was the most common diagnosis in those individuals with back pain and bacterial infection, and there was a relationship between the presence of bacteria and low back pain with disc herniation [8]. Based on these results, our trial will examine the efficacy of antibiotic treatment in individuals with chronic low back pain and disc herniation confirmed on MRI. There is a potential with restricting our criteria to those with Modic changes that we could miss a subgroup of patients that may benefit from antibiotics. However, to determine the role of Modic changes, we will include people with and without Modic changes and determine whether the presence of Modic changes predicts those individuals more likely to respond to antibiotic treatment.

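### The article says the analyses will adjust for medication used during the trial, but its Statistical analysis section adjusts only for baseline values; on-trial medication should stay out of the efficacy models

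*Protocol article*

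**What the plan says.** The subsection Concomitant medication use (Methods, Potential explanatory factors) opens: "The use of non-opioid analgesics and non-steroidal anti-inflammatory drugs will be allowed during the trial". It then lists treatments among the things that randomisation makes similar between groups, and closes: "We will also collect data on the medication used and adjust for this in the analyses". It limits this neither to use at baseline nor to a supplementary or sensitivity analysis. The Anthropometry subsection just before it does specify baseline.

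Data collection for economic evaluation records the amount and type of medication at baseline and at 3, 6, 9 and 12 months, so post-randomisation data will exist.

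The Statistical analysis section describes a different model. Continuous outcomes are analysed by intention to treat, using "linear regression adjusting for the baseline of the outcome variable". Supplementary analyses adjust for imbalanced baseline factors. The Modic interaction model adjusts for baseline values of the outcome. Medication appears in none of these.

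The Discussion says the authors expect "usual care to be balanced across the treatment groups due to randomisation".

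**The concern.** Analgesic and NSAID use during follow-up comes after randomisation, and people in more pain tend to take more of it. If the antibiotic lowers pain, the antibiotic arm will tend to use less. Medication is then a consequence of the treatment effect. Putting it in the model compares patients with equal medication use, which removes part of the benefit from the estimate and gives up the protection of randomisation.

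The stated rationale does not help. Randomisation balances what precedes it. Treatment taken afterwards can differ between arms precisely because the study drug works.

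The stakes are real because the Background says that a finding of no effectiveness will count as strong evidence against the treatment. A model that can shrink a true benefit weakens that conclusion. Two incompatible descriptions of the model also leave room to choose between them once results are known.

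**Working it through.** **1. The plan's own figure.** The sample size section takes 85 per arm and claims that "there will be 90% power to detect a difference of 0.50 standard deviations in our primary outcome measure of pain". On the rating scale, with SD 3.0, that is 1.5 units. Alpha is not stated; I assume two-sided 0.05.
- SE = 3.0 × √(2/85) = 0.460
- 1.5/0.460 = 3.26
- power = Φ(3.26 − 1.96) = 90.3%

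The stated 90% is reproduced (90.0% with the noncentral t).

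**2. What medication adjustment does in the planned model.** Inputs from the article: true difference 1.5, SD 3.0, 85 per arm, adjustment for the baseline outcome. Assumptions, because the article gives no value:
- b is the baseline to follow-up correlation.
- r is the within-arm correlation of on-trial medication with 12-month pain. It arises because pain drives use; medication itself does not change pain.

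Take Y as 12-month pain, T as antibiotic arm, and M = r·Y/3 + √(1 − r²)·noise, so M has within-arm SD 1.
- Given arm and baseline, the slope of Y on M is 3r(1 − b²)/(1 − r²b²).
- The arm difference in M is −1.5r/3 = −0.5r.
- The adjusted effect is −1.5 + 0.5r × slope = −1.5 × (1 − r²)/(1 − r²b²).

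With b = 0.5:

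| r | (1 − r²)/(1 − r²b²) | Adjusted effect (units) | Shrinkage |
|---|---|---|---|
| 0.1 | 0.99/0.9975 = 0.992 | 1.49 | 1% |
| 0.3 | 0.91/0.9775 = 0.931 | 1.40 | 7% |
| 0.4 | 0.84/0.96 = 0.875 | 1.31 | 13% |
| 0.5 | 0.75/0.9375 = 0.800 | 1.20 | 20% |

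With no baseline term (b = 0) the factor is 1 − r², giving 1.36, 1.26 and 1.13 for r = 0.3, 0.4 and 0.5 (9%, 16%, 25%). That is not the planned model.

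**3. Power in the same model.** The residual SD is 3 × √[(1 − b²) × factor].
- Without medication, b = 0.5: SD = 3 × √0.75 = 2.598; SE = 2.598 × √(2/85) = 0.399; power = Φ(1.5/0.399 − 1.96) = 96%.
- With medication, r = 0.5: SD = 3 × √(0.75 × 0.80) = 2.324; SE = 0.356, or 0.359 after allowing for the correlation between arm and medication; power = Φ(1.20/0.359 − 1.96) = 92%.
- The same steps give 95% for r = 0.3 and 94% for r = 0.4.
- With a weaker baseline correlation, b = 0.3, power goes from 93% to 84% at r = 0.5.

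**4. A second, different model.** I simulated 400,000 patients per scenario. Medication was a yes/no variable used by about half the patients and driven by mid-trial pain. The regression was adjusted for baseline (correlation 0.5), and the mid-trial to 12-month residual correlation was 0.7. All of these are assumptions.

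| Loading of medication on pain | Medication lowers pain by | Effect without medication in model | Effect with it |
|---|---|---|---|
| 0 | 0 | −1.50 | −1.50 |
| 0.3 | 0 | −1.50 | −1.46 |
| 0.5 | 0 | −1.52 | −1.39 |
| 0.7 | 0 | −1.49 | −1.23 |
| 0.3 | 1.0 | −1.44 | −1.46 |
| 0.7 | 1.0 | −1.37 | −1.24 |

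Shrinkage runs from about nil to 18%. Where medication depends weakly on pain but relieves it strongly, the shift is negligible and slightly in the other direction. With no antibiotic effect, both models gave about 0 throughout.

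**The case against.** The strongest reply is that the Statistical analysis section already defines the primary model, and medication is not in it. The sentence on medication sits in a list of explanatory factors and names no particular analysis. A sponsor who simply follows the Statistical analysis section gets an unaffected primary result. This stands in part: a reader might infer that the primary result is bound to be biased, and the article does not support that. It does not dispose of the point. The medication sentence is unqualified, it follows directly on drugs allowed during the trial, and nothing ranks one section above the other. This is a conflict between two stated decisions, and not a detail left to an analysis plan.

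A reader might also infer that power drops from 90% to between 80% and 87%. Those figures come from a model without the baseline covariate. In the planned model, with a baseline correlation of 0.5, power stays at about 92% to 95% for r from 0.5 down to 0.3. It falls below 90% only under less favourable assumptions, such as b = 0.3 with r of 0.4 or more.

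Nor does the material show a risk of false positives. In the scenarios checked, bias needed both a real antibiotic effect and pain-driven medication use.

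Finally, it would go too far to bar on-trial medication from every analysis. A clearly labelled sensitivity analysis is legitimate.

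**Conclusion.** The point holds as a conflict between two sections, one of which commits to conditioning on a post-randomisation variable. Confidence is high on the conflict, and on the principle that a model including on-trial medication does not estimate the total intention-to-treat effect. Confidence is low on size, because the article gives neither the baseline correlation nor the link between medication and pain. Under the assumptions b = 0.5 and r = 0.3 to 0.5, a true 1.5-unit effect is reported as about 1.40 to 1.20. With weak dependence the loss is close to nil. The likely harm is an understated benefit, and it arises only if the medication sentence is carried into the efficacy models.

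**What to change.** Four wording changes, made before the 12-month data are analysed:

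1. State that the primary analysis and the Modic interaction analysis follow the Statistical analysis section and do not include medication used during the trial.
2. Limit any medication adjustment in the efficacy models to use recorded at baseline.
3. Confine on-trial medication to a description by arm or to a clearly labelled sensitivity analysis that is not presented as the intention-to-treat effect.
4. In Concomitant medication use and in the Discussion, correct the statements that randomisation balances treatment taken after it. Randomisation balances prior treatment; later use may differ as a result of the study drug.

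The cost is editing only. Medication is already collected at baseline and at each follow-up, and no visit, sample size or data item changes. The Trial status section has 12-month outcomes running to 27 May 2022, so on the article's own timetable the clarification can precede the analysis.

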#### Compensation status

For each individual, we will record whether their back pain is associated with a compensation claim, and if so the nature of the claim, including the type, duration, items approved and associated costs.

#### Adverse events

We will monitor for adverse events through regular blood tests to assess participants’ kidney and liver function (2, 6 and 12 weeks), as well as asking participants a series of clinical questions, including whether they have seen a doctor, been to a hospital or experienced any new symptoms. Research staff will also request that participants spontaneously report adverse events to them if they occur. If an adverse event is reported, we will record the type, frequency and severity of the event, including whether it is considered to be unrelated or associated with the study drug.

### Data collection for economic evaluation

Cost data will be measured using cost questionnaires completed by participants at baseline and 3, 6, 9 and 12 months of follow-up. The questionnaires will refer to a previous period of not more than 3 months to prevent issues with recall bias. The cost questionnaires will include information on all health care utilisation due to chronic low back pain, such as the number and type of medical and allied health visits, imaging usage, amount and type of medication (using The Medication Quantification Scale [22]), other care/assistance (i.e. home-care assistance) and hours of absenteeism from paid and unpaid work. Unit costs of resources will be obtained from the Australian Pharmaceutical Benefits Scheme’s manual of costs. The Short form Health and Labour questionnaire will allow data on absenteeism from paid work, production losses without absenteeism from paid work and hindrance in the performance of paid and unpaid work to be collected [16]. The cost questionnaires and questionnaire data will be recorded during phone contact.

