### Economic analysis

An economic evaluation will be performed in conjunction with the clinical trial to investigate the cost-effectiveness and cost-utility of amoxicillin-clavulanate compared with placebo. The economic evaluation will be conducted from a societal and health care perspective and all relevant costs will be included. Costs of the antibiotic treatment will be included, along with costs of other health care utilisation, such as other prescription medication, care by general practitioners, allied health professionals and medical specialists, hospitalisation and professional home-care. Costs for patients and their family will also be measured. Finally, costs of productivity loss due to paid and unpaid work will also be included. Pain will be primary outcome measures in the cost-effectiveness analysis. For the cost-utility analysis, utilities will be expressed as quality-adjusted life years (QALYs) as measured using the EQ-5D-5L.

The mean differences and 95% confidence intervals for total costs, costs of health care utilisation and costs of productivity loss between the antibiotic and placebo groups will be obtained by bias-corrected and accelerated bootstrapping using 5000 replications. Cost-effectiveness ratios will be estimated by dividing the difference in the total costs between the antibiotic group and the placebo group by the difference in the mean effects for pain intensity and disability. A cost-utility ratio will be determined for QALYs gained over a 12-month follow-up. To determine these ratios and uncertainty surrounding the ratios, the bias-corrected percentile bootstrapping method (5000 replications) will be applied and will be graphically presented on cost-effectiveness planes. Acceptability curves will also be used to determine the probability that the antibiotic therapy was cost-effective compared with placebo at different values of the maximum acceptable ratio.

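### The cost questionnaires are limited to care for back pain, while the economic analysis promises all relevant costs, so health care for antibiotic side effects has no stated route into the cost totals

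*Protocol article*

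**What the plan says.** Three sections of the protocol article bear on this point.

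- **Data collection for economic evaluation** names the source of the cost data: "Cost data will be measured using cost questionnaires completed by participants at baseline and 3, 6, 9 and 12 months of follow-up". It then describes their health care content by cause: "The cost questionnaires will include information on all health care utilisation due to chronic low back pain". The examples are medical and allied health visits, imaging, medication and home help. No other source of health care use is named for costing.
- **Economic analysis** sets the scope of the evaluation: "The economic evaluation will be conducted from a societal and health care perspective and all relevant costs will be included". It continues: "Costs of the antibiotic treatment will be included, along with costs of other health care utilisation, such as other prescription medication". The list goes on to general practitioners, allied health professionals, specialists, hospitalisation and home care, with no restriction to back pain.
- **Adverse events**, as part of safety monitoring, asks participants questions "including whether they have seen a doctor, been to a hospital or experienced any new symptoms". For each reported event, "we will record the type, frequency and severity of the event, including whether it is considered to be unrelated or associated with the study drug". The section does not mention costs.

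Two other places matter. The secondary outcomes section describes the productivity questionnaire as covering work lost through ill health or injury in general. The Discussion accepts that side effects, liver injury in particular, are possible with a three-month course and that adverse events need consideration.

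**The concern.** An economic evaluation of a drug has to count the care that the drug causes as well as the care that it averts. As described, the plan counts the drug cost and any back-pain care averted, but gives no route for care that the drug induces. A participant answering a question about care for back pain would properly leave out a consultation for a gastrointestinal or liver problem.

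This omission would not necessarily be neutral between arms. Side effects of the active tablet can arise only in the active arm, so that is where an excess of such care would be expected if there is one. The numerator of each ratio is the difference in total costs, and a cost missing mainly from one arm feeds directly into it. The cost-utility analysis has a further mismatch. QALYs come from the EQ-5D-5L, which the article uses as a measure of general health, so a side effect can lower the QALYs while the cost of treating it is not counted.

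**Working it through.** The article states no figure on this point, so there is none to reproduce. The check compares the sections and then derives the direction of any error.

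**1. Scope comparison**

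| Item | Data collection for economic evaluation | Economic analysis | Adverse events |
|---|---|---|---|
| Doctor visit for back pain | collected | costed | asked about |
| Doctor visit for a side effect | outside the stated scope | within the stated scope | asked about, no link to costing |
| Hospital care for a side effect | outside the stated scope | within the stated scope | asked about, no link to costing |
| Medication for a side effect | outside the stated scope | within the stated scope | not mentioned |
| Work lost to a side effect | not clearly excluded (general productivity questionnaire) | within the stated scope | not mentioned |

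Rows two to four are the gap. The section on concomitant medication also says that data on medication used will be collected, but for adjustment in the analyses, not for costing.

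**2. Direction of the error**

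Let pA and pP be the proportions of patients needing side-effect care in the antibiotic and placebo arms, and cA and cP the mean cost of that care per patient affected. If this care is not costed:

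- true cost difference = recorded cost difference + δ, where δ = pA × cA − pP × cP;
- for a positive effect difference ΔE, the ratio of costs to effects is too low by δ / ΔE;
- net benefit at willingness to pay λ is λ × ΔE − ΔC, so it is overstated by δ at every λ, and with it the acceptability curve.

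The error favours the antibiotic when δ > 0. It vanishes when δ = 0 and reverses when δ < 0.

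**3. Size, on assumed values only**

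The article gives neither event rates by arm nor unit costs. Taking a common cost c in both arms, δ = (pA − pP) × c. Results in currency units per patient:

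| Assumed excess pA − pP | c = 50 | c = 200 | c = 1000 |
|---|---|---|---|
| −5 points | −2.5 | −10 | −50 |
| 0 | 0 | 0 | 0 |
| 5 points | 2.5 | 10 | 50 |
| 10 points | 5 | 20 | 100 |
| 20 points | 10 | 40 | 200 |
| 30 points | 15 | 60 | 300 |

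For example, 0.10 × 200 = 20 per patient. If the true pain difference were the 1.5 units used in the sample size section, the cost per unit of pain reduction would be understated by 20 / 1.5 = 13.3. These values show how the error scales. They do not estimate it.

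**The case against.** The best defence is that the collection section describes what the questionnaires include and does not say that they exclude anything else. Its examples are plainly not exhaustive: hospitalisation, family costs and the trial drug are costed in the economic analysis section but do not appear among them. That section gives a general promise that would cover side-effect care, and the adverse-event section collects contacts that could be costed. The detail may sit in a full protocol or a health-economic plan that is not shown.

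Part of this stands. The article does not say that side-effect care will be left out, and a reader who infers that the cost-effectiveness result *is* biased goes further than the text allows. But an open list of examples does not remove the condition on cause that governs the list. The point is therefore not a missing detail: the article states a restriction in one section that conflicts with the scope stated in another.

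Three stronger readings are tempting and are not supported:

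- *The bias always favours the antibiotic.* This needs an excess of costed side-effect care in that arm. The article reports none, describes the liver risk as very low, and says that people with a risk factor for liver injury are excluded.
- *All side-effect costs are missed.* Lost productivity is measured with a questionnaire that is not confined to back pain, so the gap concerns health care costs.
- *The safety blood tests at 2, 6 and 12 weeks are a missing cost of the antibiotic.* They are described for participants generally, so as delivered they add no difference between arms. Charging them to the antibiotic alone would be a modelling choice about routine practice, and leaving it unmade is not an error in this plan.

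**Conclusion.** The point holds as an inconsistency of scope with a conditional consequence. The questionnaires as described would not supply the cost of health care for side effects, the analysis section promises all relevant costs, and no section connects the adverse-event contacts to costing. If that care remains uncosted and is dearer in the antibiotic arm, the cost difference, the cost-effectiveness and cost-utility ratios and the acceptability curves will be too favourable to the antibiotic. The size cannot be derived from the article and could be zero. It matters most if the other components of the cost difference are small.

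The conclusion rests on reading the cause restriction literally and on the absence of any other stated source of health care use for costing. It is worth correcting because cost-effectiveness is a declared aim of the trial. The pain and clinical secondary analyses do not depend on it.

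**What to change.** Make the two economic sections agree. State that doctor visits, hospital care and medication for adverse events, taken from the adverse-event records, will be costed in both arms whatever the judged relation to the study drug, and added to total health care costs. Costing both arms alike avoids relying on attribution and lets the data show whether there is an excess. Check that the records, with the concomitant medication data where needed, hold enough on quantities. Count each contact once where it also appears in the cost questionnaire.

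If the records are too coarse to cost directly, fix in advance an assumed cost per adverse-event contact and a range for it, and report the cost difference, ratios and acceptability curves with and without that cost.

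Rewording the questionnaire alone would come late: the trial status section puts the start of recruitment in September 2015 and the end of randomisation in May 2021, so much of the cost data was already collected. Using the existing safety records takes some extra costing work, with no new patients, visits or procedures. The cost-effectiveness section of the report should state which route was taken.
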